### Statistical methods

All quantitative analyses will be undertaken in IBM SPSS Statistics Version 22.0 by the research fellow and trial statistician.

#### Changes over time

In order to explore stability in the primary outcome measures over the treatment period, and change in satisfaction, quality of life, mood and illness and treatment beliefs, multilevel models (MLM) will be employed. Time will be nested within participants and to check the assumption that scores within a participant are highly correlated, the first MLM will include no predictors and a scaled identity covariance type for both level 1 and level 2 in order to calculate the intraclass correlation coefficient (ICC). Models will be fitted with a first order autoregressive (AR1) covariance structure. Restricted Estimate Maximum Likelihood (REML) methods will be used as these are preferred for smaller samples [35].

Trial arm (0 = control, 1 = intervention), time (0, 1, 2) and the interaction between trial arm and time will be entered as fixed effects in each model, with participant identification number as a random effect. A significant interaction term will be interpreted as evidence for differential treatment effectiveness. Pairwise comparisons will be performed in order to establish where the significant differences lie, using estimated marginal means and standard errors. Standardised adjusted effect sizes for group differences at each time point will be calculated using Hedges’ *g* along with 99 % confidence intervals (as *p* < 0.01) using the formula provided by Turner and Bernard [36]. Hedges’ *g* includes a correction factor for small samples which, if absent, may lead to a less accurate and upwardly biased effect size. These effect sizes are interpreted in the same way as Cohen’s *d* [37] (small = 0.20, medium = 0.50, large = 0.80).

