### Randomisation

Randomisation (1:1) will be undertaken by a central randomisation service by the data management team at Moorfields Eye Hospital (MEH) in order to ensure the research fellow collecting and analysing the data is blinded to group allocation. Participants will be randomised to receive either treatment as usual or patient-initiated follow-up appointments. Randomly permutated blocks of varying sizes will be employed to ensure balance between treatment groups. Due to the nature of the nurse-led botulinum toxin clinic it will not be possible to blind the treating healthcare professionals from group allocation. The trial co-ordinator will staff the telephone line that participants in the intervention group will use to book their appointments and, as such, the trial co-ordinator will not be blinded to group allocation.

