### Outcomes

Participants will be in the trial for 9 months. An initial baseline assessment will be taken by a research fellow prior to randomisation; this will include the full range of measures. Self-report measures will be taken again at 3- and 9-month follow-ups.

At baseline, demographic information will be collected using self-report measures including: date of birth, gender, marital status, ethnicity, postcode, number of years of schooling, highest completed level of education and further education. Data will also be collected from the patients’ medical notes on diagnosis, year of diagnosis, duration of botulinum toxin treatment, number of previous cycles, frequency of previous cycles, last dose, and co-morbidities. The total number of botulinum toxin injections and dosage received by the patient across the trial period will be collected.

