### Sample size

Sample size for multilevel modelling (MLM) was estimated by simulating a range of scenarios using the software Power and Precision™ (Version 4.1; [32]). Using a large ICC of 0.3 [33], time as nested within participants, and setting power at 80 %, it was estimated that between 92 and 230 participants would be required with small to medium effects (Table 2). Based on a 79 % completion rate [9] this would mean that between 112 (56 per group) and 278 (139 per group) will need to be consented into the trial.

**Table 2 Tab2:** Sample size estimation based on four scenarios with small to medium effect sizes

Scenario	Effect size (*d*)	ICC	Standard care	Intervention	Time points	Alpha	Tails	Power
Scenario 1	0.25	0.3	115	115	4	0.05	2	0.80
Scenario 2	0.3	0.3	80	80	4	0.05	2	0.80
Scenario 3	0.35	0.3	59	59	4	0.05	2	0.80
Scenario 4	0.4	0.3	46	46	4	0.05	2	0.81

The qualitative study assessing acceptability of the new service aims to recruit an initial sample of 10 participants with a stopping criterion of a further three interviews to confirm that data saturation has been achieved [34]. Data saturation is defined as the emergence of no new themes in relation to the research question.

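### Leaving the pre-randomisation baseline free to differ by arm costs the interaction test about 35–47% of its precision at the planned ICC of 0.3, and less if the correlation is higher; AR(1) on unequally spaced visits is a separate, smaller fault

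*Protocol article*

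**What the plan says.** All references are to the protocol article.

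- **Changes over time** sets the fixed effects. Besides trial arm, "time (0, 1, 2) and the interaction between trial arm and time will be entered as fixed effects in each model". Participant is a random effect and estimation is by REML. The covariance sentence reads: "Models will be fitted with a first order autoregressive (AR1) covariance structure". A significant interaction is to be read as evidence that the arms differ in effectiveness. Pairwise comparisons of estimated marginal means and a Hedges' g at each time point follow. Neither a baseline covariate nor a common baseline mean is mentioned.
- **Outcomes** places time 0 before allocation: "An initial baseline assessment will be taken by a research fellow prior to randomisation; this will include the full range of measures". Self-report measures are repeated at 3 and 9 months.
- **Randomisation** gives 1:1 allocation.
- **Sample size** gives the only correlation in the article: "Using a large ICC of 0.3 [33], time as nested within participants". The first row of Table 2 is "Scenario 1 0.25 0.3 115 115 4 0.05 2 0.80".

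**The concern.** Randomisation makes the true arm difference at time 0 zero. The planned model estimates that difference anyway, and the interaction subtracts the estimate from the difference at follow-up. All the sampling noise of the baseline comparison therefore enters the test. A model that uses the known equality, or adjusts for baseline, weights the baseline by its correlation with follow-up and never does worse in large samples. The weaker the correlation, the more the plain change contrast loses. The sample size section plans on a correlation at which the loss is substantial.

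The covariance is a second, independent matter. AR(1) on codes 0, 1, 2 forces the 0-to-3-month and 3-to-9-month correlations to be equal and the variance to be constant, although one gap is twice the other. If that pattern is wrong, model-based standard errors of individual contrasts are wrong too.

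**Working it through.** **Inputs.** From the article: ICC 0.3, d = 0.25, 115 per arm and two-sided alpha 0.05 (Table 2, Scenario 1); visits at 0, 3 and 9 months. Assumptions of this check: equal correlation r between all visits, unit SD, the same effect d at both follow-ups, normal approximation.

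**The plan's own figure.** Table 2 behaves like a comparison of arm means averaged over four measurements. The variance factor is (1 + 3 × 0.3)/4 = 0.475, SE = √(2 × 0.475/115) = 0.0909, d/SE = 2.75 and power 0.785, against the stated 0.80. Scenarios 2 to 4 give 0.786, 0.788 and 0.795 (stated 0.80, 0.80, 0.81). So Table 2 reproduces to within 2 points, but for an average over time and not for the interaction.

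**Variance of the arm contrast, in units of 2σ²/n.**

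- One follow-up visit: free baseline 2(1 − r); common or adjusted baseline 1 − r². Share of precision lost: (1 − r)/2.
- Mean of two follow-ups: free baseline 1.5(1 − r); common or adjusted baseline (1 + r)/2 − r². Share lost: 2(1 − r)/3.

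| r | one visit: free / adjusted (ratio) | lost | mean of two: free / adjusted (ratio) | lost |
|---|---|---|---|---|
| 0.3 | 1.40 / 0.91 (1.54) | 35% | 1.05 / 0.56 (1.88) | 47% |
| 0.5 | 1.00 / 0.75 (1.33) | 25% | 0.75 / 0.50 (1.50) | 33% |
| 0.6 | 0.80 / 0.64 (1.25) | 20% | 0.60 / 0.44 (1.36) | 27% |
| 0.7 | 0.60 / 0.51 (1.18) | 15% | 0.45 / 0.36 (1.25) | 20% |
| 0.8 | 0.40 / 0.36 (1.11) | 10% | 0.30 / 0.26 (1.15) | 13% |

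A loss of a third or more needs r ≤ 1/3 for one visit, or r ≤ 0.5 for the mean of two.

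**Power at r = 0.3, d = 0.25, 115 per arm.**

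- Mean of two visits: SE √(2 × 1.05/115) = 0.135 against √(2 × 0.56/115) = 0.099. Power is 0.456 against 0.717.
- One visit: SE 0.156 against 0.126. Power is 0.36 against 0.51.
- 2-df test: non-centrality 57.5 × 0.0625 × 2/2.10 = 3.42 against 57.5 × 0.0625 × 2/1.12 = 6.42. Power is 0.362 against 0.615.

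**Per-visit arm differences.** The pairwise comparisons at a single follow-up are unadjusted post-baseline differences, not change contrasts. Their variance is 1, against 1 − r² = 0.91, so the loss is r² = 9% at r = 0.3.

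**AR(1).** Random intercept plus AR(1) has one common adjacent-visit covariance.

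- If the truth is compound symmetry, the structure contains it and every SE ratio (model/true) is 1.00.
- If the correlation is a per 3 months of calendar time, the true adjacent correlations are a and a². The best-fitting structure puts both near their average.
  - a = 0.5: average of 0.50 and 0.25 is 0.375. The 3-month change has SE ratio √(0.625/0.50) = 1.12 and the 3-to-9-month change √(0.625/0.75) = 0.91.
  - a = 0.8: average of 0.80 and 0.64 is 0.72. The ratios are √(0.28/0.20) = 1.18 and √(0.28/0.36) = 0.88.
- With correlation 0.8·exp(−t/8), t in months, the adjacent correlations are 0.55 and 0.38, and the ratios are 1.09 and 0.93.
- For a from 0.5 to 0.8, the SE of the 9-month change is within 1% of the truth and the 2-df interaction test has size about 0.053 against 0.05.

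**The case against.** The strongest reply is that a free-baseline repeated-measures model is valid under randomisation, widely used, and a matter of preference; and that an article may leave baseline adjustment to an analysis plan that is not shown. Validity is conceded. But the article does not leave the model open: it lists the fixed effects, the random effect, the covariance and the deciding test, and applies them to each outcome. Improving a stated method with data already collected is a fair comment.

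Other parts of the reply stand and limit the point:

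- **A reader might infer that a third or more of precision is lost whatever the data.** The article does not support that. The ICC of 0.3 is a sample-size input, and the analysis section itself expects scores within a participant to be highly correlated. At 0.6 to 0.8 the loss is 10–27%.
- **A reader might blame AR(1) for the lost precision, or think it undermines the interaction test.** The loss comes only from the free baseline. The specified participant random effect removes the AR(1) misfit under compound symmetry, and under decay the overall test keeps its size. The decay curves are assumptions with no source in the article.
- **A reader might set 0.362 against 0.717 and conclude that power doubles.** That compares a 2-df test with a 1-df test. Only the matched pairs in the working are fair.
- **A reader might apply the 35–47% to the per-visit arm differences.** Those lose about 9% at ICC 0.3.
- **Scope.** The 3- and 9-month schedule is stated for self-report measures. The clinician-rated severity scale is also taken at clinic visits and by telephone two weeks after treatment, so a 3×3 layout is not established for it.
- **Target.** Making the follow-up average the primary contrast would change the question in a trial whose aim is stability over time. Statisticians could differ on that, and it is not needed here.

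**Conclusion.** The point holds as a matter of efficiency. At the planned ICC of 0.3, the deciding interaction test discards 35% of the available precision for one follow-up visit and 47% for the mean of two. At a correlation of 0.6 it discards 20% and 27%, and at 0.7, 15% and 20%. These figures assume equal correlation between visits; the power figures also assume equal effects at both follow-ups and the smallest effect in Table 2. The treatment estimate is not biased, and nothing here invalidates the trial.

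The common-baseline model would not by itself bring the interaction test to 80% power at d = 0.25 and 115 per arm. It recovers much of the shortfall without extra recruitment.

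The AR(1) choice carries less weight. It can mis-state the SE of particular contrasts (3-month change roughly 9–18% too large; 3-to-9-month change 9–12% too small for decay of 0.5 to 0.8 per 3 months, about 7% for the third curve), but only if correlation decays with calendar time.

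**What to change.** For outcomes measured at baseline, 3 and 9 months:

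1. Constrain the arms to a common mean at time 0, or use the 3- and 9-month scores as outcomes with baseline as a covariate.
2. State that time is a factor, which the planned pairwise comparisons already imply.
3. Replace AR(1) with an unstructured 3×3 covariance, keeping REML.
4. Keep the arm effects at each follow-up and their joint test as the inference.
5. State that baseline questionnaires are completed before allocation. The common-baseline constraint depends on this, and Procedures has them returned by post.

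The cost is a change of wording and SPSS syntax, and six covariance parameters instead of three, which the planned sample supports easily. No new data are needed.

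### Effectiveness is decided on the arm-by-time interaction, but the reported effect size is an arm difference at each time point with no baseline adjustment listed, so test and reported size will often give different verdicts

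*Protocol article*

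**What the plan says.** All of this is in the protocol article, Statistical methods, Changes over time, unless noted.

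- **Model.** Trial arm, "time (0, 1, 2) and the interaction between trial arm and time will be entered as fixed effects in each model", with participant as a random effect. Baseline is therefore one of the repeated outcomes (time 0), and no covariate is listed.
- **Decision rule.** "A significant interaction term will be interpreted as evidence for differential treatment effectiveness".
- **Follow-up step.** "Pairwise comparisons will be performed in order to establish where the significant differences lie, using estimated marginal means and standard errors". The contrast to be compared is not named.
- **Reported size.** "Standardised adjusted effect sizes for group differences at each time point will be calculated using" Hedges' g, with "99 % confidence intervals (as *p* < 0.01").
- **Timing of baseline** (Outcomes). "An initial baseline assessment will be taken by a research fellow prior to randomisation".
- **Planning values** (Sample size, Table 2). The smallest effect is scenario 1: d = 0.25, ICC 0.3, 115 per arm, 4 time points, two-sided alpha 0.05, power 0.80.

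**The concern.** The interaction asks whether the arms changed differently from baseline. The effect-size sentence reports how far apart the arms are at each time. In a finite sample the two differ by the arm difference at baseline. That difference is pure chance here, because baseline precedes randomisation, and the model as listed does not adjust g for it. The word 'adjusted' has no listed covariate behind it, and a g at time 0 can describe only chance imbalance.

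At stake is the reading of every outcome modelled this way. A report could show a non-significant interaction beside a clear g at 9 months, or a significant interaction with no follow-up interval excluding zero. The article would then answer whether the care model works from one contrast, and by how much from another.

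**Working it through.** **Inputs.** n = 115 per arm, d = 0.25, ICC 0.3 and two-sided alpha 0.05 (Table 2, scenario 1); times 0, 1, 2 and 99 % intervals (Changes over time). Assumed: ICC 0.5 and 0.7 as a range, unit SD, compound symmetry, complete data, known variance, time as a categorical factor (so a 2-df interaction), the interaction judged at the 5 % of Table 2, and the same effect d at 3 and 9 months.

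**1. The plan's own power figure.** Table 2 is roughly reproduced as a comparison of arm means averaged over 4 times. SD = sqrt((1 + 3 × 0.3)/4) = 0.689, and 0.25/(0.689 × sqrt(2/115)) = 2.75, which gives power of about 0.785 against the stated 0.80. The averaged difference is neither the interaction nor g at one time, so Table 2 does not settle which contrast is meant.

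**2. The two quantities.** Write D0, D3 and D9 for the arm differences in SD units.
- Interaction contrast at 9 months: D9 − D0, with SE sqrt(4(1 − ICC)/n).
- g at 9 months: D9, with SE sqrt(2/n).
- The gap is D0, with mean 0 and SD sqrt(2/115) = 0.13, about half of 0.25.

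Example with no treatment effect, D0 = 0.2 and ICC 0.3: expected g at 9 months is 0.3 × 0.2 = +0.06, and the expected interaction contrast is (0.3 − 1) × 0.2 = −0.14.

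**3. How often the verdicts differ.** (D0, D3, D9) were simulated as trivariate normal with mean (0, d, d), variance 2/n and correlation ICC. The 2-df Wald interaction test at 5 % was compared with the arm differences at 3 and 9 months, counted as positive if either has p < 0.05.

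| d = 0.25, 115 per arm | ICC 0.3 | ICC 0.5 | ICC 0.7 |
|---|---|---|---|
| Interaction not significant, a follow-up difference significant | 37 % | 27 % | 13 % |
| Interaction significant, neither follow-up difference significant | 5 % | 12 % | 25 % |
| Verdicts disagree (total) | 42 % | 39 % | 38 % |
| Interaction significant at 5 %, both follow-up 99 % intervals include zero | 14 % | 24 % | 43 % |

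The last row exceeds the second because the interval level is stricter than the test level. At d = 0.4 the total falls to 23, 13 and 8 %. At 105 per arm (266 × 0.79 = 210 completers) and d = 0.25 it is 42, 39 and 39 %.

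**4. Reporting the tested contrast instead.** If the change contrasts D3 − D0 and D9 − D0 are reported, disagreement with the 2-df test falls to 16, 16 and 12 %.

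**5. Precision at 9 months.** Standard errors at 115 per arm and ICC 0.3:
- change: sqrt(4 × 0.7/115) = 0.156
- unadjusted difference: sqrt(2/115) = 0.132
- baseline-adjusted difference: sqrt(2(1 − 0.3²)/115) = 0.126

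Change to unadjusted: sqrt(2 × 0.7) = 1.18. For 80 % power at d = 0.25, n per arm is 2(1.96 + 0.84)²/0.25², about 252, times 2(1 − ICC) for change or 1 − ICC² for the baseline-adjusted difference. At ICC 0.3, 0.5 and 0.7 this gives 352, 252 and 151 for change, and 229, 189 and 129 for the baseline-adjusted difference.

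**The case against.** Four points can be made for the plan.

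- **Same target.** A reader might infer that g and the interaction measure different effects. They do not: with a pre-randomisation baseline the expected arm difference at time 0 is zero, so D9 and D9 − D0 have the same expectation. At ICC 0.3 the unadjusted difference is even the more precise. This stands. The conflict comes from chance imbalance and unequal precision.
- **The pairwise step.** A reader might also infer that the pairwise comparisons are of arms at each time point. The article does not name that contrast; only the effect-size sentence refers to group differences. A condensed article may leave such detail to the full plan. This stands, so the point rests on the effect-size sentence.
- **Model-based means.** It would go too far to call the reported differences raw arm means. They come from a REML mixed model, and with 79 % completion the 9-month means borrow from earlier scores. 'Adjusted' may mean just that. What can be said is that no baseline covariate is listed.
- **Low power and common practice.** Simple effects after an interaction test are usual, and much of the disagreement is one p-value crossing a threshold while the other does not. At ICC 0.3 the interaction has 36 % power and the 9-month difference about 47 %. Significant 9-month results in opposite directions occur in roughly 1 in 80,000 trials or fewer. This stands as a limit on the word 'contradict'. It does not remove the point, because matching the contrast cuts disagreement from 42, 39 and 38 % to 16, 16 and 12 %.

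**Conclusion.** The point holds in a limited form and is of moderate weight. The article fixes the decision rule, the model and the effect size in the same section, and the effect size does not belong to the tested contrast. This is a mismatch in stated text, so it is not simply detail left to an unseen analysis plan.

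At the smallest planned effect and 115 per arm, test and follow-up arm differences give different verdicts in about four trials in ten; at d = 0.4 it is between 8 and 23 %. The percentages rest on the assumptions listed with the calculation. In particular, if the interaction were also judged at 1 %, the figures for 99 % intervals beside a 5 % test would not apply, but the mismatch of contrasts would remain. Neither bias nor opposite estimands follows from the text.

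**What to change.** In Changes over time, report the effect size and its interval at 3 and 9 months for the contrast that is tested, at the same alpha as the test. There are two ways:

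1. **Preferred:** use a baseline-adjusted arm difference for both the test and the effect size. The baseline scores are already collected, and the estimate is more precise than the change contrast or the unadjusted difference. The cost is a change to the primary test, to be documented before unblinding.
2. **Minimal:** keep the interaction test and report the arm-by-time contrasts (arm difference in change from baseline). This needs only a different contrast statement in the same model. The cost is an interval about 18 % wider than that of the unadjusted difference at ICC 0.3, and some remaining threshold disagreement with the omnibus test (16, 16 and 12 %).

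Either way, state that the pairwise comparisons are of that same contrast, treat the time-0 difference as descriptive only, and write 'adjusted' only if baseline enters the estimate. No data collection changes.

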**Methods/Design:**

A randomised controlled trial will compare a patient-initiated model of care, where patients determine botulinum toxin treatment timing, to the standard model of care in which care is scheduled by the clinical team. A sample of 266 patients with blepharospasm or hemifacial spasm will be recruited from Moorfields Eye Hospital (MEH), London. The trial will be accompanied by a mixed-methods evaluation of acceptability of the new service. Patients who meet eligibility criteria will be assessed at baseline and those in the intervention group will be provided with instructions on how to book their own treatment appointments. Patients in both groups will be followed up 3 and 9 months into the trial and all patients will be returned to usual care after 9 months to meet safety protocols. Primary outcome measures include disease severity (questionnaire), functional disability (questionnaire) and patient satisfaction with care (questionnaire). Secondary outcomes include disease-specific quality of life (questionnaire), mood (questionnaire), illness and treatment perceptions (questionnaire and semi-structured interviews), economic impact (questionnaire) and acceptability (questionnaire and semi-structured interviews).

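### The sample size assumes two-sided alpha 0.05, but the analysis section names only p < 0.01 and gives the deciding interaction test no level; if 0.01 governs, the stated 80 % power becomes about 57 to 59 %

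*Protocol article*

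**What the plan says.** **Sizing.** The Sample size section of the protocol article works by "setting power at 80" per cent and concludes that "between 92 and 230 participants would be required with small to medium effects". Table 2 ("Sample size estimation based on four scenarios with small to medium effect sizes") lists alpha 0.05, two tails, in every row. Its first row reads "Scenario 1 0.25 0.3 115 115 4 0.05 2 0.80" and its last "Scenario 4 0.4 0.3 46 46 4 0.05 2 0.81". Each row has one effect size and no allowance for several outcomes.

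**Primary outcomes.** The Abstract states: "Primary outcome measures include disease severity (questionnaire), functional disability (questionnaire) and patient satisfaction with care (questionnaire"). The Outcomes section identifies them as the JRS, the BSDI and the CSQ.

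**Analysis.** Changes over time fits a multilevel model to each outcome. It treats a significant interaction between arm and time as evidence that the treatments differ in effectiveness, without naming the level. Pairwise comparisons follow. Hedges' g for the group difference at each time point is then reported "along with 99 % confidence intervals (as *p* < 0.01"). No other significance level appears under Statistical methods.

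**The concern.** The article uses 0.05 to size the trial and 0.01 to report it, and does not connect the two. The word introducing the 0.01 presents it as a level already in force and as the reason for the 99 % intervals, yet it is not set anywhere earlier in the article.

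The gap falls on the decision rule for the primary outcomes. An interaction with p = 0.03 is a positive finding if the level in the Sample size section applies, and a negative one if the level in the analysis section applies. The choice could be made after the results are known. Each choice also has its own cost: a trial with less power than published, or intervals that do not correspond to the tests.

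**Working it through.** **Inputs.** From Table 2: d = 0.25, 0.30, 0.35, 0.40; n per arm = 115, 80, 59, 46; ICC 0.3; 4 time points; two-sided alpha 0.05; power 0.80, 0.80, 0.80, 0.81. From Sample size: 79 % completion. From the Abstract: 266 recruited. From Randomisation: 1:1 allocation.

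**Step 1: reproduce Table 2.** The software's routine is not shown. I took a comparison of participant means over m = 4 measures with equal correlation:

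- variance factor = (1 + (m − 1) × ICC)/m = (1 + 3 × 0.3)/4 = 0.475
- power = Φ( d / √(2 × 0.475/n) − z )

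For d = 0.25 and n = 115, the first term is 0.25/√(0.95/115) = 2.75. At alpha 0.05 (z = 1.960), power = Φ(0.79) = 0.785. All four rows come within 2 points of the stated figures.

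**Step 2: change alpha alone.** At alpha 0.01, z = 2.576.

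| d | n per arm | stated power | recomputed, alpha 0.05 | recomputed, alpha 0.01 |
|---|---|---|---|---|
| 0.25 | 115 | 0.80 | 0.785 | 0.569 |
| 0.30 | 80 | 0.80 | 0.786 | 0.570 |
| 0.35 | 59 | 0.80 | 0.788 | 0.572 |
| 0.40 | 46 | 0.81 | 0.795 | 0.582 |

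Starting from exactly 80 % at 0.05 instead, power at 0.01 is Φ(1.960 + 0.842 − 2.576) = Φ(0.226) = 0.589. Like for like, the drop is therefore 80 % to 59 %, or 78.5 % to 57 %.

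**Step 3: the planned size.** 266 × 0.79 = 210.1, or 105 per arm. The standard error is √(0.95/105) = 0.0951. At alpha 0.01:

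| d | d/0.0951 | power |
|---|---|---|
| 0.25 | 2.63 | 0.521 |
| 0.30 | 3.15 | 0.718 |
| 0.35 | 3.68 | 0.865 |
| 0.40 | 4.21 | 0.948 |

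For d = 0.25 at alpha 0.05, the same formula gives 0.748.

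**Step 4: what 80 % power at alpha 0.01 would take.** The detectable effect with 115 per arm is (2.576 + 0.842) × √(0.95/115) = 3.417 × 0.0909 = 0.31. To keep d = 0.25, the sample would have to grow by ((2.576 + 0.842)/(1.960 + 0.842))² = 1.49, so 115 per arm becomes about 171.

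**Step 5: the other reading, 0.05 for each primary outcome.** For three independent outcomes, with success declared on any one, the family-wise error is 1 − 0.95³ = 0.143. At 0.01 each it is 1 − 0.99³ = 0.030. At 0.05/3, power for d = 0.25 with 115 per arm is 0.639.

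**The case against.** The strongest reply is that the 0.01 qualifies only the Hedges' g intervals, which come after the interaction test and the pairwise comparisons. A coherent reading exists: the interaction is tested at 0.05, and stricter 99 % intervals are used for the several follow-up comparisons. Table 2 would then stand. So a reader might infer that the two sections cannot both hold, or that the trial simply has 57 % power, but the article supports neither. It attaches no level to the interaction, and the lower power follows only if 0.01 governs.

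Three further points on that side stand.

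- The formula is for a group difference averaged over four measures. The deciding test is an arm-by-time interaction, whose power cannot be derived from the stated inputs. The 57 to 59 % shows what changing alpha does to Table 2's type of calculation; it is not the power of the planned test.
- The article gives a range of effects and no single target. At 105 completers per arm, power at 0.01 still exceeds 80 % for d = 0.35 and 0.40.
- The 14 % is an upper value. The Functional disability section reports good convergent validity between BSDI and JRS, so the outcomes are not independent. Nor does the article say that one significant outcome of three makes the trial positive; the closing Discussion frames success jointly. A multiplicity procedure may be in an analysis plan that is not shown, so its absence from the article is not itself the point. The 0.01 may even be an unstated guard against multiplicity.

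What the reply does not remove is that the article states two levels and does not say which one decides. A later analysis plan could choose between them. If it chose 0.01, the published power would be wrong; if it chose 0.05, the 99 % intervals would still need a reason.

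**Conclusion.** The point holds in conditional form, and the text is wrong as written: alpha is 0.05 in the sample size and 0.01 in the analysis, with nothing reconciling them and no level on the test that decides effectiveness.

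- If 0.01 governs, power on Table 2's own inputs is about 57 to 59 %, not 80 %. At the planned size it is about 52 % for the smallest effect considered. The loss comes from alpha alone, not from having three outcomes.
- If 0.05 governs, a group difference with p between 0.01 and 0.05 would be called significant while its 99 % interval included zero. The family-wise error would be at most about 14 %, under independence and an any-one-counts rule.

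These are alternatives and should not be added together. The power figures assume equal correlation of 0.3 between measures, four measures and an average group difference.

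**What to change.** State one significance level for the interaction tests on JRS, BSDI and CSQ that accounts for there being three of them. Either 0.01 for each outcome, or family-wise 0.05 by a named procedure such as Holm, would do; the choice is the investigators'. Report confidence intervals at the matching level, or say why the follow-up comparisons use a stricter one. Restate Table 2's power or detectable effect at the chosen level: at alpha 0.01 with 115 per arm, about d = 0.31 for 80 % power; at 0.05/3, the first Holm step, about 64 % power for d = 0.25.

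The change should be made before allocation is unmasked. It costs a few sentences, a recalculated table and a less favourable power statement. No extra patients are needed, provided the restated power or detectable effect is accepted.
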